### Diagnostic methods

2.5

All patients will undergo clinical and anamnestic data collection procedures (patient interview for identification of chief complaints, past medical history, and performing external obstetric examination) (Table 1).

**Table 1 tab1:** Timeline of procedures within the project.

	Procedures	Before cesarean section (preoperative)	During cesarean section (intraoperative)	After cesarean section (postoperative)
1	Clinical and anamnestic methods	+	−	−
2	Laboratory tests	+	+	+
3	US/MRI diagnostics	+	−	−
4	Pathohistological examination	−	−	+

Laboratory tests (common blood test, biochemical blood test, coagulation tests, and thromboelastography) will be performed following the general examination. Thromboelastography (TEG) will be carried out at the transfusiology department of UMC using the TEG5000 Haemonetics 2017 thromboelastograph. A thromboelastograph is a device used to assess the mechanical strength of clot formation using the interaction between coagulation factors and platelets, which cannot be assessed in other laboratory methods such as coagulation tests (30, 31). A blood test for thromboelastography will be taken at the following time points (1) the preoperative period (24 h before surgery); (2) 10 min after fetal extraction; (3) immediately after closing the skin wound; and (4) 24 h after surgery. The key TEG parameters include reaction time (R), clot formation time (K), maximum amplitude (MA), alpha angle (*α*), percent lysis 30 min after MA (Ly30), and coagulation index (CI; a calculated index of total coagulation).

Assessing the risk of coagulation will help to predict thromboembolic complications in the postoperative period and recommend adequate thromboprophylaxis.

Ultrasound investigation will be used to confirm the diagnosis of PAS disorders. The main ultrasound signs of placenta accreta include placental lacunae, disappearance of the normal hypoechoic retroplacental zone, abnormal structure of the border between the uterus and the bladder wall, and a pathological pattern of blood flow with color Doppler mapping. Loss of the hypoechoic retroplacental zone and subplacental hypervascularization is more common in placenta increta, while vascular lacunae and “uterine hernia” are associated with placenta percreta. Ultrasound diagnostics will be carried out using a Philips ultrasound machine, equipped with a 9.4 Hz vaginal probe and a 5.1 Hz convex probe with Doppler.

Magnetic resonance imaging (MRI) of the pelvic organs without contrast is used to confirm the diagnosis and degree of placenta accreta, particularly in cases where the placenta is located on the posterior wall, in suspected placenta percreta, unsatisfactory visualization (in obese women), and to determine angiometric parameters of the abdominal aorta before endovascular intervention. MRI will be carried out using the PHILIPS Ingenia 3.0T device.

Pathohistological examination of the placental and eventual resected uterine tissue will be performed after cesarean section to confirm placenta accreta spectrum syndrome (32, 33). The histological examination will confirm the diagnosis of placenta accreta by extended areas of missing decidua between the placenta and myometrium. These may include an area with placental villi affixed directly to the myometrium or abnormal implantation with a coating of fibrinoid and intervening trophoblast between the placental villi and the myometrium. In cases of placenta accreta, differentiation between decidual cells and extravillous trophoblastic cells can be challenging. The myometrium is typically not thinned in such cases. In contrast to placenta accreta, in cases of placenta increta, the presence of chorionic villi within the myometrium with thinning of the myometrium is expected. For placenta percreta, no remaining myometrium is identified, and dye is present in tissue obtained from areas suspicious for placenta percreta. Invasion through the myometrial wall is observed in the area of percreta or villous tissue adjacent to extrauterine structures (bladder) (32, 33).

### Interventions

2.6

#### REBOA

2.6.1

In the operating room, a patient will be positioned on the operating table (supine position). After appropriate sanitation of the surgical field, under local anesthesia S. Lidocaine 1% – 10 mL, the right common femoral artery will be punctured under ultrasound guidance. An introducer of the appropriate diameter will be installed and washed with heparinized saline. A compliant or semi-compliant balloon of the appropriate diameter will be installed into the lumen of the aorta Zone IIIa (proximal zone), (Figure 2) under ultrasound guidance. After that, a team of obstetricians will perform a cesarean section and extraction of the fetus. At the time of fetus extraction, the balloon will be inflated in the lumen of the aorta with a saline solution using a 20-mL injection syringe (16, 34–36). Manual control for the absence of pulsation in the common femoral arteries on both sides will be performed for the control group. The maximum inflation time of the balloon will be 15 min. If necessary, the balloon can be inflated repeatedly, with a break of 5 min between periods of aortic occlusion. At the end of the main stage of the operation, the balloon will be deflated step by step under the control of invasive blood pressure measurement. The introducer will be removed using suturing devices and manual compression of the puncture site for 10 min. An aseptic pressure bandage will be applied at the end.

**Figure 2 fig2:**
[figure not shown]
Schema showing REBOA balloon placement in aortic zone IIIa (proximal zone).

#### Cesarean section

2.6.2

Surgery will be performed according to the standard procedure following the national guideline on “Cesarean section” used in the NRCMC (37).

In order to avoid operator variability and differences in surgical techniques, the same persons (team of researchers) will be involved in surgical procedures for both groups (cases and controls).

### Ethical considerations

2.7

All potential study participants will receive an explicit explanation of the study aims, procedures, and potential outcomes. After the detailed explanations written informed consent will be obtained from patients who agree to participate in this study. The study was approved by the Institutional Ethical Board of the University Medical Center on 10.11.2023, protocol #2023/01-028.

### Patient withdrawal

2.8

Any study participant who no longer agrees to participate in this study can withdraw at any moment without consequences for their subsequent healthcare. These patients will be managed according to the approved national guidelines (25, 37). Data of patients who decided to withdraw from the study will not be analyzed.

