### Study design and study environment

2.1

This will be a prospective, randomized controlled trial (RCT) that will investigate the superiority of REBOA in combination with cesarean section compared to the traditional cesarean section for pregnant women with PAS disorders. The study was registered in the Clinical.Trials.gov database (registration ID NCT06721182) and will take place in the National Research Center for Mother and Childcare (NRCMC), University Medical Center (UMC), Astana, Kazakhstan. The NRCMC is a tertiary care leading specialized institution in the field of obstetrics and gynecology in Kazakhstan. The hospital has sufficient experience in the field of scientific research and a powerful technical and personnel base.

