### Recruitment process

2.3

The study participant recruitment will be performed from December 2024 to December 2025. Subjects who meet the eligibility criteria will be randomly assigned to either the intervention/case group (cesarean section + REBOA) or to the traditional treatment/control group (cesarean section). To ensure the control group patients’ safety, intraoperative bleeding will be managed according to the national guidelines for the pathology of the placenta (25) and postpartum bleeding management.

A simple randomization method will be applied (Figure 1). Randomization will be based on a “single sequence of random assignments known as simple randomization” (27). This technique maintains complete randomness of the assignment of a person to a particular group. The randomization procedure includes using a shuffled deck of cards (odd - intervention group, even – control group) (27). The randomization will be performed after patient recruitment, once the study aims and expected outcomes are explained to the patient and informed consent is obtained, by the responsible project team member.

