Future clinical and research implications. The measurable outcome of endovascular management includes the assessment of maternal intra- and postoperative complications. Major complications associated with endovascular balloon occlusion include distal ischemia, reperfusion syndrome, thrombosis, and lower extremity embolization will be analyzed and discussed in comparison with the results from previous studies. The outcomes of this research will facilitate improvements in the local guidelines on the management of placenta previa and PAS disorders. Moreover, the study results may contribute to the development of new guidelines that should prioritize the practical realities faced by developing countries, including limited access to advanced imaging, specialized surgical teams, and blood transfusion resources.

Study strengths and limitations. This will be the first study in Kazakhstani obstetric practice to investigate the efficacy of endovascular balloon occlusion for the management of pregnancy complicated by PAS disorders. The prospective randomized controlled study design will be the major strength of the study, as it will help define the difference between the two approaches (cesarean section vs. cesarean section and REBOA). A limitation of the study, however, will be the small sample size. However, due to the low prevalence of PAS disorders, the complexity of the study, and budget limitations, this sample size has been determined as appropriate based on the sample size calculation. Another limitation will be the lack of blinding for outcome assessors. However, the nature of the investigation and management procedures does not allow for blinding (45). Therefore, this study is planned as an open-label, where patients, clinicians, and care providers are aware of management (cesarean section + REBOA vs. cesarean section) allocations.

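### Section 2.8 drops all data from women who withdraw, which removes randomised patients, including some with outcomes already recorded, and can bias the comparison

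*Protocol article*

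**What the plan says.** Section 2.8 (Patient withdrawal) of the protocol article lets women leave at any time: "Any study participant who no longer agrees to participate in this study can withdraw at any moment". It then fixes how their data are handled: "Data of patients who decided to withdraw from the study will not be analyzed". It does not separate declining the assigned procedure from refusing use of one's data, and it does not keep what was collected before withdrawal.

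Three other places set the context.

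- Section 2.3 (Recruitment process) puts consent before allocation: "The randomization will be performed after patient recruitment, once the study aims and expected outcomes are explained to the patient and informed consent is obtained".
- The Discussion describes the blinding: "this study is planned as an open-label, where patients, clinicians, and care providers are aware of management".
- Section 2.1 describes a randomised trial "that will investigate the superiority of REBOA in combination with cesarean section compared to the traditional cesarean section".

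Section 3.1 measures the primary outcome, blood loss, from suction volume and weighed swabs in theatre. Hysterectomy is a secondary outcome, also settled during the operation. Section 2.4 sets 72 women per group from the hysterectomy calculation, with no allowance for withdrawals.

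**The concern.** A woman can withdraw only after joining the study, and allocation comes straight after consent, so in practice most withdrawals would follow randomisation. She then knows her arm. Every participant has also consented to the balloon as a condition of entry, so a woman allocated to control may be disappointed and a woman allocated to REBOA may have second thoughts. Either may leave after a difficult operation. Withdrawal can therefore be related to arm, to prognosis or to the outcome itself.

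Once such women are removed, the remaining groups are no longer those that randomisation formed. The article counts the randomised design as its major strength, and this rule weakens that protection. The loss is hardest to justify for a woman who withdraws after surgery, because her blood loss and hysterectomy status already exist and would be discarded.

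**Working it through.** The article gives no figure for the effect of withdrawals, so the check has two parts: what the rule covers, and how much it could matter under stated assumptions.

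**What the rule covers.** Sections 2.8, 2.3 and the Discussion together give exclusion without limit, withdrawal possible at any time, randomisation after consent, and known allocation. Nothing elsewhere in the article overrides the exclusion. It therefore reaches randomised women, before or after their outcomes are recorded.

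**Back-solving the hysterectomy rates.** Section 2.4 gives OR 0.31, two-sided alpha 0.05, power 80% and about 72 per group, but not the control rate p1. Its formulas are

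- p2 = 0.31·p1 / (1 − p1 + 0.31·p1)
- n = (1.96 + 0.84)² · [p1(1 − p1) + p2(1 − p2)] / (p1 − p2)²

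At p1 = 0.305, p2 = 0.120 and n = 72.5. At p1 = 0.307, p2 = 0.121 and n = 72.1. A second solution exists at p1 = 0.879, p2 = 0.693. The stated 72 can therefore be matched but not independently reproduced. The figures below use 30.5% and 12.0%, a difference of 18.5 points, as an assumption.

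**Bias with no true effect (hysterectomy).** Assumptions: 30% of women are higher grade with risk 0.60, and 70% are lower grade with risk 0.179. Overall risk is 0.3·0.60 + 0.7·0.179 = 30.5% in both arms. In the control arm 15% of lower-grade women withdraw; in the REBOA arm 15% of higher-grade women withdraw.

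- Control, remaining: (0.3·0.60 + 0.595·0.179) / 0.895 = 32.0%
- REBOA, remaining: (0.255·0.60 + 0.7·0.179) / 0.955 = 29.1%
- Spurious difference: −2.9 points

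About 64 controls and 69 REBOA women remain. Exact enumeration of the chi-square test gives a rejection probability of 7.0%, against 5.3% at those sizes with no bias.

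**Bias with no true effect (blood loss).** The SD implied by Section 2.4 is 1331.46 / 2.06 = 646 mL. Suppose a fraction w of the REBOA arm only withdraws, and these women would have lost d mL more than average. The spurious difference is −w·d / (1 − w). At w = 10%, it is −56 mL for d = 500 and −111 mL for d = 1000. With standard error 646·√(1/72 + 1/64.8) ≈ 111 mL, type I error is about 8% and 17%.

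**Bounds on unseen outcomes.** Assume 7 of 72 withdraw per arm (about 10%) and the 65 analysed per arm show 30.5% and 12.0%, that is 19.825 and 7.8 expected events, 12.025 apart.

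- All seven REBOA withdrawals and no control withdrawals have hysterectomy: (12.025 − 7) / 72 = 7.0 points, a shift of −11.5
- The reverse: (12.025 + 7) / 72 = 26.4 points, a shift of +7.9

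**Power for hysterectomy** (exact enumeration of the chi-square test, 30.5% vs 12.0%):

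| Analysed per arm | Power |
|---|---|
| 72 | 79.6% |
| 68 | 76.7% |
| 65 | 74.6% |
| 61 | 72.4% |

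**The case against.** The best defence is that the rule may rarely operate. The operation is elective and the primary outcome is complete when it ends, so withdrawal before measurement can fall only between allocation and surgery, an interval the article does not give. The wording concerns women who no longer agree to take part. It does not reach protocol deviations or ordinary missing data. If nobody withdraws, the rule does nothing. Where a woman refuses use of her data, exclusion may be unavoidable. The modelled bias of about −3 points is also modest, although the pattern was chosen to be adverse. All of this stands and limits the severity. It does not justify discarding outcomes already recorded for women who have not refused their use.

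Several stronger readings are tempting but not supported.

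- A reader might infer that a randomised woman who later needs an emergency section is also excluded. Section 2.2 lists that as an eligibility criterion and does not say it is applied after randomisation.
- A reader might fault the article for naming no intention-to-treat set. Analysis sets are commonly left to the full protocol or analysis plan, which are not shown. The problem is the exclusion that is stated.
- A reader might conclude that allocation should be drawn closer to surgery. That is a separate design preference, and Section 2.3 does not fix the day.
- A reader might take 30.5% and 12.0% as planned rates. They are back-solved.

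**Conclusion.** The point holds as a defect in a stated rule. Section 2.8 as written removes randomised women whatever the timing, arm or reason, and can bias an open-label comparison if withdrawal is related to arm or surgical course. Bias is possible, not demonstrated: its size and direction cannot be known from the article.

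The illustrations rest on assumed withdrawal rates and patterns and, for hysterectomy, on assumed risks. They range from little effect, if few withdraw, to the shifts shown for 7 of 72 per arm. The −11.5 and +7.9 limits are extremes, since each requires every withdrawal in one arm and none in the other to have hysterectomy. The power loss concerns hysterectomy, a secondary outcome. For blood loss, Section 2.4 reports a need for only 3 women per group, so the concern there is bias rather than power.

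This should be fixed, but it does not invalidate the design.

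**What to change.** Replace the last sentence of Section 2.8 with wording such as:

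*All randomised patients are analysed in the group to which they were randomised. Data collected up to withdrawal are kept and analysed, and routinely recorded surgical data are used, unless the patient explicitly withdraws permission for use of her data.*

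Report withdrawals by arm with reasons, and add a best/worst-case sensitivity analysis for hysterectomy.

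The cost is a change to protocol and consent wording, since consent terms govern whether data can be kept. One gap would remain. A woman who withdraws before surgery is managed under national guidelines, and nothing in the article says that swabs are weighed outside the study, so her measured blood loss may be unavailable. The change should not be presented as free of any data-collection issue for those women.

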### Statistical analysis

2.9

Statistical analyses will include both descriptive and inferential methods. Baseline characteristics of the study population will be summarized as mean ± standard deviation (SD) or median with interquartile range (IQR) for continuous variables, and as frequencies and percentages for categorical variables. Inferential analyses will compare group differences in major outcomes using independent samples *t*-tests for normally distributed data or Mann–Whitney U-tests for non-normally distributed data. Categorical outcomes will be assessed using Pearson’s χ^2^ test or Fisher’s exact test, as appropriate. For multi-group comparisons, one-way analysis of variance (ANOVA) or Kruskal–Wallis tests will be used, depending on data distribution.

To quantify the effect of REBOA while adjusting for potential confounders, regression models will be used for continuous outcomes, and classification models will analyze categorical outcomes such as hysterectomy or complications. Python will be used for statistical analyses, with Statsmodels (v0.14.4), SciPy (v1.11.3), and Scikit-learn (v1.3.0) libraries for inferential statistics and modeling; NumPy (v2.1.3) and Pandas (v2.1.1) for data handling; and Matplotlib (v3.8.1) and Seaborn (v0.13.2) for data visualization.

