### Outcomes

3.1

The *primary outcome* will be blood loss during cesarean section. Blood loss will be measured with reference to the collected blood in the suction flask in the surgical theater and the weighted surgical swabs.

The following will be measured as *secondary outcomes*:

Directly linked to the intervention’s effectiveness: (1) occurrence of hysterectomy during cesarean section, (2) blood transfusion volume, (3) duration of surgery, (4) balloon application time, (5) stay in an intensive care unit (ICU), (6) complications (thrombotic events, pain, early and delayed surgical complications), and (7) total days of postsurgical hospital stay;Indirectly reflect the intervention effectiveness: neonatal outcomes – (8) Apgar score and (9) admission to neonatal ICU.

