### Study subjects sociodemographic and clinical characteristics

3.2

Based on the study participants’ sociodemographic and clinical data, descriptive statistics will be calculated and presented (Table 2).

**Table 2 tab2:** Demographic and clinical data.

Variable	Intervention group	Control group	*p*-value
Age (years)			
Gestational age			
Gravidity			
Parity			
Abortions (spontaneous and artificial)			
Prior history of cesarean sections			
Prior history of uterine surgery			

PAS, placenta accreta spectrum.

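### The data choose between a t-test and Mann–Whitney for blood loss, and no single primary analysis in mL is fixed

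*Protocol article*

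**What the plan says.** Section 3.1 (Outcomes) says that the primary outcome "will be blood loss during cesarean section". Section 2.4 plans this outcome on a pooled mean difference of −1331.46 mL.

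Section 2.9 (Statistical analysis) then gives two layers of analysis:

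- **Two-group tests.** "Inferential analyses will compare group differences in major outcomes using independent samples" t-tests where the data are normal, or "Mann–Whitney U-tests for non-normally distributed data". Categorical outcomes get Pearson's chi-square "test or Fisher’s exact test, as appropriate".
- **Adjusted models.** For outcomes such as blood loss the plan reads: "To quantify the effect of REBOA while adjusting for potential confounders, regression models will be used for continuous outcomes". For the yes/no outcomes it uses a different label: "classification models will analyze categorical outcomes such as hysterectomy or complications".

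The section does not rank the layers. It does not name the covariates, or the model and effect measure for hysterectomy. Table 2 (Section 3.2) includes "Prior history of cesarean sections" among the baseline variables. Section 2.5 plans ultrasound, with MRI, before surgery.

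**The concern.** A t-test and a Mann–Whitney test answer different questions. The first concerns the difference in mean blood loss in mL, which is what the trial is planned on. The second concerns whether a patient in one arm tends to rank above a patient in the other, and it gives no estimate in mL. Under the stated rule the question is settled only once the data are in.

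Blood loss is often right-skewed, so the switch could well operate. If REBOA also changes the spread of blood loss, the rank test can point somewhere that the mean does not. A significant primary result could then be read as a saving in mL that the data do not show.

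The unranked regression adds a second candidate for the main result. For hysterectomy, the adjusted analysis has a label that covers both effect-estimating models and purely predictive ones.

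**Working it through.** **1. The planning target.** Section 2.4 uses n = 2(1.96 + 0.84)² (SE² + τ²) / Δ². From the printed CI, SE = (1643.21 − 1019.71)/(2 × 1.96) = 159.06. Reading 292106.16 as τ² itself (it is printed with a further square), n = 2 × 7.84 × (25300.08 + 292106.16)/1331.46² = 2.81 per group, as the article states. The quantity planned on is thus a mean difference in mL.

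**2. How often the switch would operate.** The article gives no normality criterion and no patient-level SD. Assumptions: Shapiro–Wilk at 5% in each arm, both arms having to pass for a t-test; 72 per arm; mean 2500 mL; SD 1331.46/2.06 = 646 mL for the normal case; log-normal otherwise. There were 5,000 simulated trials without an effect and 2,500 with a mean reduction of 0.467 control SDs. That is the difference detectable with 80% power: (1.96 + 0.84) × √(2/72).

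| Assumed blood loss | Sent to Mann–Whitney (no effect) | Type I error of the rule | Tests disagree, no effect | Tests disagree, effect | Power, t / Mann–Whitney |
|---|---|---|---|---|---|
| Normal | 10.7% | 5.0% | 1.7% | 5.6% | 81.2% / 78.8% |
| Log-normal, CV 0.15 | 45.9% | 5.1% | 2.3% | 6.2% | 82.9% / 81.2% |
| Log-normal, CV 0.26 | 84.8% | 5.3% | 2.4% | 6.2% | 84.5% / 83.5% |
| Log-normal, CV 0.5 | 99.9% | 5.4% | 4.7% | 6.7% | 88.9% / 91.0% |
| Log-normal, CV 0.8 | 100% | 4.6% | 4.1% | 5.2% | 93.1% / 96.7% |

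**3. Equal means, unequal spread.** Take log-normal blood loss with mean 2500 mL in both arms and CV 0.8 against 0.4.

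- Simulation: the rule rejects in 42% of trials and the t-test in 5.4%. Repeat runs gave 44% against 6.5%, and 44% against 5.4%.
- Check by formula: the log variances are ln(1 + 0.8²) = 0.495 and ln(1 + 0.4²) = 0.148. With equal means, the log means differ by (0.495 − 0.148)/2 = 0.173. The chance that a patient from the less variable arm bleeds more is Φ(0.173/√0.643) = Φ(0.216) = 0.585.
- The null SE of this quantity is √(145/(12 × 72 × 72)) = 0.0483, so the expected z is 0.0855/0.0483 = 1.77 and the rejection rate is about Φ(1.77 − 1.96) = 0.42. This agrees with the simulation.
- Direction: the medians are 2500/√1.64 = 1952 mL (CV 0.8) and 2500/√1.16 = 2321 mL (CV 0.4). The rank test therefore counts against the less variable arm, although the means are equal.

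**4. What adjustment could add.** With SD 646 mL, SE = 646 × √(2/72) = 107.7 mL and the detectable difference is 302 mL. Adjustment multiplies both by √(1 − R²). The detectable difference becomes 286 mL at R² = 0.1, 253 mL at 0.3 and 213 mL at 0.5. The documents give no R². The planned 1331.46 mL is already 1331.46/107.7 = 12.4 SEs, so power there is about 100% with or without adjustment.

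**The case against.** The strongest reply is that an article condenses a fuller plan. The normality criterion, covariate list, model type and effect measure are commonly left to a statistical analysis plan, so their absence alone is no fault. That stands. The point rests instead on what Section 2.9 does state: a test chosen by the observed distribution, beside a second analysis of the same outcome with no order between them.

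It is also fair that the switch hardly moves the type I error when both arms share one distribution (4.6% to 5.4%). The harm lies in what is being estimated.

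A reader might infer more than the text supports:

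- **That blood loss is analysed without adjustment and precision is thrown away.** Section 2.9 plans regression for continuous outcomes expressly to quantify the REBOA effect.
- **That hysterectomy will have no usable adjusted effect.** Logistic regression fits the label classification model, Statsmodels is listed for inference, and a chi-square or Fisher test is planned as well. The wording is loose; it is not shown to be wrong.
- **That histological grade will be a covariate.** Section 2.5 says "Pathohistological examination of the placental and eventual resected uterine tissue will be performed after cesarean section", to confirm the diagnosis. Nothing proposes adjusting for it.
- **That the p-value column in Table 2 will pick the covariates.** No text links the two.
- **That power is being lost.** Simulated gains, such as 59% for the t-test, 66% for Mann–Whitney and 80% for adjusted log regression, assume a 25% reduction, CV 0.8 and R² of 0.25. None of these is in the article.

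**Conclusion.** The point holds in this form: the stated rule lets the data choose the target of the primary comparison, and the article does not say whether that test or the adjusted regression is primary. Under the stated assumptions, skewed blood loss would nearly always lead to Mann–Whitney, which neither estimates nor tests a difference in mL. If spread also differs between arms, the rule can reject in 42–44% of trials with equal means, against 5.4–6.5% for the t-test. That figure depends on the assumed log-normal shape and on CVs of 0.8 and 0.4. It illustrates what the rule can do and does not forecast this trial.

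The case rests on the estimand. It does not rest on inflated type I error under a common distribution, on missing adjustment or on lost power. The hysterectomy wording needs clarifying but is the lesser part.

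**What to change.** In Section 2.9, or in an analysis plan finalised before the outcome data are examined:

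- Remove the distribution-driven choice of test for blood loss.
- Name one primary analysis: linear regression of blood loss in mL on arm with fixed preoperative covariates. These are the number of prior caesareans and, if it is recorded for every patient, the preoperative ultrasound/MRI PAS grade. Report the adjusted mean difference in mL with a 95% CI from robust standard errors.
- Keep Mann–Whitney and a log-scale analysis as sensitivity analyses. A log-scale primary would itself leave the mL target.
- For hysterectomy, replace the classification-model wording with logistic regression on the same covariates, reported as an odds ratio and a standardised risk difference, each with a 95% CI.

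The cost is wording. Prior caesarean history is already in Table 2. The imaging grade is not listed there, and Section 2.5 directs MRI particularly to selected cases, so it must be confirmed that a grade exists for all patients before it is named. The small downside is some power when blood loss is strongly skewed. In the unadjusted simulations above, the mL-scale test had 88.9% against 91.0% for Mann–Whitney at CV 0.5, and 93.1% against 96.7% at CV 0.8.
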